## IV. MEDICAL DEONTOLOGY

### 4.1. Ethics and Review Committee (ERC) / Ethics for Scientific Research Committee (ESRC)

To start the implementation of the clinical trial protocol in the service unit, it is necessary to obtain the declaration of the Institutional Ethics Committee, which grants the certification after making its assessments and corresponding analyses that the document (version 1.0):

- ✓ Complies with the Helsinki Declaration (Ethical principles for medical research in humans, adopted by the World Medical Assembly, Fortaleza, Brazil, 2013).
- ✓ Complies with the norms and ethical criteria established in national and international ethics and legal regulations code in force in Cuba (Guidelines for Good Clinical Practices, CECMED 2000, Cuba; Guide to Good Clinical Practices of the International Conference for Harmonization – ICH E-6).
- ✓ Includes the protection of the rights and wellbeing of the patients involved.
- ✓ Appropriately describes the selection criteria of the patients.

### 4.2. Ethical issues for the implementation of the trial

The retrospective study is properly endorsed from the ethical viewpoint due to the following reasons:

- a. It is approved by the ERC/ESRC. At the same time, as a contribution to the transparency of the research, the protocol will be published in the Cuban Public Registry of Clinical Trials.
- b. A clinical intervention on the patients will not be carried out; their evolution will be observed as soon as they are treated with the Jusvinza drug. There is evidence of the reduction of inflammation in patients with COVID-19 treated with Jusvinza. The treatment with Jusvinza has been safe for the

Approved by:

[name] [name]

Signature:

[figure not shown]

Cargo:

Director of Biomedical Research, CIGB

Date:

13/05/2021

patients. The molecular studies made in Cuba, during the extension of the use of Jusvinza to all hospitals with COVID-19 patients, have confirmed the results obtained during the compassionate use study, demonstrating that the Jusvinza treatment is able to reduce inflammation in COVID-19 patients. The administration of Jusvinza in severely ill patients prevents the progress to the critical stage of the disease. The effectiveness of the treatment in severely ill patients surpasses 85%.

- c. The results obtained from processing the information of patients treated with Jusvinza will produce a benefit for the COVID-19 patients that will undergo the treatment in the future.
- d. The integrity of the participants in the research will be respected, ensuring the confidentiality of all the data of the patients.

#### **4.3. Instructions for obtaining the informed consent**

Does not apply.

#### **4.4. Ethical responsibilities of all participants in the study**

**Researcher:** Offers access to the information of the patient recorded in the Clinical Records

**Institution:** Ensures the maintenance and appropriate use of the facilities by the researchers and submits the protocol to the approval of the Ethics and Review Committee (facilitated by the researcher in charge).

**Research team:** Ensures the compliance of the assigned responsibilities.

**Promoter:** Ensures the reliable collection of the information, while providing confidentiality to the data of the patients.

**Ethics and Review Committee:** Reviews and approves the protocol of the trial, ensuring the protection of the rights of the patients involved in the study and providing the public assurance of that protection. Verifies the progress of the study and the adherence of the researchers to the protocol.

---

Approved by:

[name] [name]

Signature:

[figure not shown]

Cargo:

Director of Biomedical Research, CIGB

Date:

13/05/2021

## V. GENERAL CONCEPT

### 5.1 Design of the trial

A retrospective, observational, monocentric study will be carried out with the primary aim of evaluating the effect of Jusvinza in the reduction of inflammation and the safety of its intravenous administration.

All patients with available information that have been treated with Jusvinza, according to the action protocol, between March 21 and July 29 of 2021, will be included.

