|---------------------------------------|----------------------------------------------------------------------------------------------------------------------------------------------------------------------------------------------------------------------------------------------------------------------------------------------------------------|
| Design of the study                   | Retrospective, observational, monocentric study
We will collect the retrospective information of each patients using the clinical records as the source of primary information, as well as clinical laboratory results and radiologic imaging stored in the GALEN program of the participating institution. |
| Number of patients                    | We will include all positive patients to SARS-CoV-2 by RT-PCR with the available information, classified as of high-risk, severe and critical conditions, who were prescribed the use of Jusvinza.                                                                                                             |
| Frequency and duration of the therapy | According to the indications of the Action Protocol                                                                                                                                                                                                                                                            |
| Drug under study                      | Drug: Jusvinza (2.5 mg or 1.25 mg), intravenous administration.                                                                                                                                                                                                                                                |
| Safety evaluation                     | 

• Symptoms

• Vital signs

• Analytical results

• Imaging results

                                                                                                                                                                        |

---

Approved by:

[name] [name]

Signature:

[figure not shown]

Cargo:

Director of Biomedical Research, CIGB

Date:

13/05/2021

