## VI. SELECTION OF THE SUBJECTS

### 6.1. Universe of patients

The universe is formed by adult patients that live permanently in Cuba (with full constitutional rights), that are positive to SARS-CoV-2 according to the RT-qPCR, who are hospitalized at [name] Díaz Soto hospital and have been prescribed the treatment with Jusvinza, according to the action protocol, in the period of March 21 to July 29, 2021.

Approved by:

[name] [name]

Signature:

[figure not shown]

Cargo:

Director of Biomedical Research, CIGB

Date:

13/05/2021

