## 6.2. Inclusion criteria

- 1) Patients  $\geq 19$  years of age.
- 2) Patients positive to SARS-CoV-2 according to the confirmatory RT-qPCR test, who are either moderately, severely, critically ill or dead, and have been prescribed the treatment with Jusvinza, in the period from March 21 to July 29 of 2021.
- 3) Patients that have not died in the first 48 hours of hospitalization.
- 4) Patients that have not been included in other clinical trials.

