## XI. STATISTICS

### 11.1 Number of patients planned

We consider as the number of patients, all those having information according to this study, at the [name] Díaz Soto Hospital and complying with the inclusion criteria.

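### Having available information is an undefined entry condition missing from the eligibility criteria, and it could shift the recovery percentages in either direction

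*Protocol*

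**What the plan says.** Three places make information a condition of entry:

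- Section 5.1: "All patients with available information" who received Jusvinza in the period March 21 to July 29, 2021.
- Summary, row on number of patients: "We will include all positive patients to SARS-CoV-2 by RT-PCR with the available information".
- Section 11.1: "We consider as the number of patients, all those having information according to this study". The sentence goes on to require, as well, that the inclusion criteria are met.

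Two places define the population without it:

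- Section 6.1 takes hospitalized, PCR-positive adults who "have been prescribed the treatment with Jusvinza, according to the action protocol" in the same period.
- Section 6.2 lists four criteria: age; a positive test with severity class, prescription and period; survival ("Patients that have not died in the first 48 hours of hospitalization"); and no participation in another trial.

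The main variables in 8.1.1 are the percentages recovering among high-risk, severe and critical patients, after seven, ten and fifteen days of treatment respectively. Sections 3.3 and 8.2 tie therapeutic success to 90% of the high-risk patients.

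**The concern.** The wording in 11.1 joins the information condition to the inclusion criteria, so it is an additional selection rule. It decides who is in the denominator, yet it is absent from the section meant to hold such rules, and its content is not given. It could mean that a clinical record can be found, that a baseline is recorded, that the outcome at day 7, 10 or 15 is recorded, or that biomarkers and imaging exist. Two abstractors working from the same files could build different cohorts.

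In a prospective study such a condition might be settled before the outcome. Here abstraction is retrospective, so whoever judges availability can normally see how the patient fared. Section 5.3, on reducing bias, relies on prior discussion among specialists and adherence to good clinical practice, and does not address selective inclusion. No section asks for a count of prescribed patients who were left out.

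At stake is the reading of a simple percentage against a fixed 90%. A modest change in the denominator can move it to either side of that line.

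**Working it through.** **1. The text.** The condition appears in the Summary, 5.1 and 11.1, and is absent from 6.1 and 6.2. None of the five places defines it. None says that the record must be complete.

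**2. Figures to reproduce.** There are none. The protocol states no sample size, share of missing records or expected loss, so what follows is illustration only.

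**3. Inputs.**

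- Threshold: 90% of high-risk patients (3.3 and 8.2).
- p, recovery observed among included patients: assumed.
- m, share of otherwise eligible patients left out for lack of information: assumed.
- q, recovery among those left out: assumed.

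**4. Formula.** Overall recovery = p(1 − m) + qm. The worst case has q = 0, giving p(1 − m). The best case has q = 1, giving p(1 − m) + m.

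**5. Results with p = 90%.**

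| m | Worst case (q = 0) | q = 50% | q = 70% | q = 90% | Best case (q = 1) |
|---|---|---|---|---|---|
| 5% | 85.5% | 88.0% | 89.0% | 90.0% | 90.5% |
| 10% | 81.0% | 86.0% | 88.0% | 90.0% | 91.0% |
| 20% | 72.0% | 82.0% | 86.0% | 90.0% | 92.0% |

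For example, at m = 10%: 0.90 × 0.90 = 0.81, and 0.81 + 0.10 = 0.91. With q = 90% nothing changes, whatever m is.

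**6. Crossing the threshold in either direction.**

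- Downward: with p = 92%, m = 10% and q = 70%, overall recovery is 0.92 × 0.90 + 0.70 × 0.10 = 0.898, or 89.8%. The break-even is q = (0.90 − 0.828)/0.10 = 72%.
- Upward: with p = 89%, m = 10% and q = 100%, overall recovery is 0.89 × 0.90 + 0.10 = 0.901, or 90.1%.

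**7. How demanding the worst case is.** For the worst case to reach 90%, p must be at least 0.90/(1 − m). That is 94.7% for m = 5% and 100% for m = 10%, and it is unattainable for m = 20%. The bounds are therefore informative only if few patients are missing, which is itself a reason to count them.

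**The case against.** The strongest reply is that the phrase is harmless. Section 1.9 uses similar language for the data source, so it may mean only that a clinical record exists to be abstracted, and a patient with a partial record would then be included. A reader might infer that recovery will be computed on patients with complete records only. The documents do not say so, and that reading should not be pressed.

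Several further points on this side stand:

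- The restriction is stated openly in three places. Nothing shows an intention to conceal exclusions, and nothing prevents the team from reporting them.
- No section links availability to transfer, length of stay or death. Deaths in the first 48 hours are already excluded by 6.2, and the second criterion there expressly admits patients who died. Any dependence on outcome is a possibility, not a documented fact.
- Data collection is scheduled for May to September 2021, close to the treatment window and at one hospital, so heavy loss of records is not evident.
- Simply deleting the phrase would not work. Without a usable record, neither the 6.2 criteria nor the severity class can be verified, and the patient cannot be assigned to any of the three percentages.
- Handling of missing values may be left to an analysis plan, which is not at hand.

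The last point does not dispose of the matter. Who enters the study belongs in the protocol, and this protocol has fixed it with an undefined term. An analysis plan cannot restore patients who were never abstracted. Nor does the benign reading rescue the text, since nothing in it rules out the stricter one.

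**Conclusion.** The point holds as a fault of definition and placement with a possible effect on the main result. An undefined condition, missing from 6.1 and 6.2 and applied at abstraction, governs the denominators of all three main percentages and the comparison with 90%.

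A reader might go further and conclude that the reported recovery will be too high. The documents do not support that. The direction depends on how those left out fared relative to those included, and this is unknown. The size is equally open: the range of 81% to 91% rests on an assumed 10% left out and an assumed 90% observed, and its ends suppose that none or all of those left out recovered. The threshold part of the argument applies only to high-risk patients, because the protocol sets no threshold for the recovery percentages of the severe and critical groups.

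The change is worth making before abstraction is complete, since it affects what can be concluded about the 90% criterion.

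**What to change.** 1. In 5.1, 11.1 and the Summary, replace the information condition with: every patient whose records allow the 6.2 criteria and the severity class to be verified. State that a missing outcome, biomarker or imaging result is not a reason for exclusion.
2. Identify candidates from the hospital's records of patients prescribed Jusvinza in the window. Report the number left out, with reasons. Those whose eligibility or class cannot be verified can only be counted, not assigned to a percentage.
3. Keep included patients with a missing outcome in the denominator. Beside each observed percentage, give the worst case (missing counted as not recovered) and the best case (missing counted as recovered). For the high-risk group, state whether the conclusion about 90% is the same across both. The worst case need not decide success: it is too low whenever any patient with a missing outcome recovered. The table layout can go in the analysis plan.

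The cost is one patient listing and a few extra table lines. The protocol names clinical records, laboratory results and stored imaging as sources but no prescription or dispensing list, so the effort of building the listing should be confirmed with the hospital. The downside is a percentage that may be less favourable or less certain.

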### 5.2 Identification of the patients

Each patient will be identified by a code that indicates the “consecutive inclusion number”, followed by the initials of the name/or names and surnames of the patient. This identification must be contained in the documents corresponding to each patient. For example, for the first patient included in the study, the identification code is 001-XYZM, where X is the initial of the first name, Y is the initial of the middle name (if there is one), Z is the initial of the first surname and M is that of the second surname.

### 5.3 Factors that may be introduced to reduce bias

- ❖ Before preparing this protocol, there was an exchange of ideas with specialists linked to the management of the use of Jusvinza in COVID-19 patients at the Central Military Hospital [name] Díaz Soto and the researchers of the Clinical Research Division, and of the Biomedical Research Division of the CIGB. The clinical experiences of the use of Jusvinza in COVID-19 patients were presented and discussed. This has made it possible to endorse the research and define the present experimental design.
- ❖ The analysis and discussion of the protocol, and its proficiency, will favor the adherence and compliance of the GCP by all researchers.

## VI. SELECTION OF THE SUBJECTS

### 6.1. Universe of patients

The universe is formed by adult patients that live permanently in Cuba (with full constitutional rights), that are positive to SARS-CoV-2 according to the RT-qPCR, who are hospitalized at [name] Díaz Soto hospital and have been prescribed the treatment with Jusvinza, according to the action protocol, in the period of March 21 to July 29, 2021.

Approved by:

[name] [name]

Signature:

[figure not shown]

Cargo:

Director of Biomedical Research, CIGB

Date:

13/05/2021

## 6.2. Inclusion criteria

- 1) Patients  $\geq 19$  years of age.
- 2) Patients positive to SARS-CoV-2 according to the confirmatory RT-qPCR test, who are either moderately, severely, critically ill or dead, and have been prescribed the treatment with Jusvinza, in the period from March 21 to July 29 of 2021.
- 3) Patients that have not died in the first 48 hours of hospitalization.
- 4) Patients that have not been included in other clinical trials.

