### III. OBJECTIVES

#### 3.1. General Objective

- To observe its effectiveness in the reduction of hyper-inflammation and the safety of the administration of Jusvinza in patients having COVID-19 whose condition was classified as moderate, severe and critical.

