## VIII. EVALUATION VARIABLES

### 8.1. Protocol variables

#### 8.1.1. Main variables

#### ❖ Evaluation of the anti-inflammatory effect:

Approved by:

[name] [name]

Signature:

[figure not shown]

Cargo:

Director of Biomedical Research, CIGB

Date:

13/05/2021

- ✓ We will calculate the percentage of high-risk patients recovering after a seven-day treatment with Jusvinza.
- ✓ We will calculate the percentage of severely ill patients recovering after a ten-day treatment with Jusvinza.
- ✓ We will calculate the percentage of critically ill patients recovering after a fifteen-day treatment with Jusvinza.

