## 8.2. Criteria for the success or failure of the individual, and of the therapy

- ☐ We will consider an **individual success** if the patient recovers; if there are no severe adverse events with a demonstrated causality.
- ☐ We will consider a **therapeutic success** if the hypothesis is demonstrated, in which 90% of the high-risk patients treated with Jusvinza do not reach the severe phases of the disease and then recover.
- ☐ We will consider an **individual failure** when a patient progresses toward a more severe condition or death and if there is a definitive interruption of the treatment due to the presence of severe adverse events, with a causal relationship attributable to the product under study.
- ☐ We will consider a **therapeutic failure** when patients progress towards the more severe stages of the disease.

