### 11.2 Plan for the statistical analysis

#### 11.2.1 Set of data analyzed

There are two groups:

***“Treated with Jusvinza”***: defined as the patients that have been treated with Jusvinza, according to the the information in their clinical records.

***“Not treated with Jusvinza”***: defined as the patients that do not have any information in their clinical records of having been treated with Jusvinza.

.

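### Inclusion criterion 3 drops treated patients who die within 48 hours of admission, which raises the recovery percentages and removes those deaths from the safety description

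*Protocol*

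**What the plan says.** **Entry.** Section 6.2, criterion 3, admits only "Patients that have not died in the first 48 hours of hospitalization". Criterion 2 of the same section takes confirmed cases "who are either moderately, severely, critically ill or dead" who were prescribed Jusvinza in the study period, so death as such does not bar a patient from entry.

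**Stated population.** Section 5.1 says that the study includes "All patients with available information that have been treated with Jusvinza" under the action protocol in that period. It sets no survival condition, and neither does the universe in Section 6.1.

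**Denominator.** Section 11.1 gives no figure. It counts all patients with information who are "complying with the inclusion criteria". In Section 11.2.1 the treated group is "defined as the patients that have been treated with Jusvinza, according to the" clinical records, and a second group consists of patients with no record of treatment.

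**Outcomes.** The first main variable in Section 8.1.1 reads "We will calculate the percentage of high-risk patients recovering after a seven-day treatment with Jusvinza". Parallel percentages follow for severe patients (ten days) and critical patients (fifteen days). Section 8.2 places individual failure at the point "when a patient progresses toward a more severe condition or death", joined to a clause on stopping treatment for related severe adverse events. It sets the therapeutic success threshold of 90% for high-risk patients only.

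**Safety.** The general objective in Section 3.1 includes "the safety of the administration of Jusvinza in patients having COVID-19". Section 9.1 grades a death related to an adverse event as Grade 5.

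**The concern.** Eligibility depends on the outcome. Death is the clearest form of non-recovery, and criterion 3 removes a defined part of the deaths before any percentage is calculated. The main variables are single-group percentages, so nothing offsets a loss that falls only on failures.

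The same patients leave the safety description. If a patient is dosed on arrival and dies the next day, that death is not described or assessed for causality, whatever its cause.

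An analysis plan written for the included patients could not repair this, because the excluded patients are not in the study data. The protocol gives no reason for the criterion, and Section 5.3 on reducing bias does not mention it.

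**Working it through.** The protocol has no sample size calculation or early-death figure to reproduce. The check has three parts: who leaves, what that does to a percentage, and what it does to safety.

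**1. Who leaves.** The window runs from hospitalization, not from first dose. The cases below are illustrative.

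| Case | Status under criterion 3 |
|---|---|
| Dosed on arrival, dies 40 h after admission | Out |
| First dosed on day 5, dies 12 h after that dose | In |
| Prescribed, dies within 48 h of admission before any dose | Out, but says nothing about the drug |

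The first two rows show that the rule does not secure a minimum exposure: the patient with the longer time since first dose is the one excluded. The third row arises because Sections 6.1 and 6.2 select on prescription, whereas Sections 5.1 and 11.2.1 speak of treatment. The arithmetic below therefore concerns dosed patients only.

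**2. Effect on a recovery percentage.** Take N dosed patients in a severity class, R recovered, and E deaths within 48 h of admission. Write p = R/N and e = E/N. None of the E patients is in R, so

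- all dosed patients: p = R/N
- under criterion 3: R/(N - E) = p/(1 - e)

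The second is never smaller than the first. The document does not give e, so all values below are assumed. The 60% is also an illustration, not a protocol figure.

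| True recovery | e = 5% | e = 10% | e = 15% |
|---|---|---|---|
| 60% | 60/95 = 63.2% | 60/90 = 66.7% | 60/85 = 70.6% |

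In reverse, the rate in all dosed patients is the reported rate × (1 - e). The starting values are the two rates in Section 3.3, 85% (severe patients) and 90% (expected in high-risk patients).

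| Reported | e = 1% | e = 2% | e = 5% | e = 10% |
|---|---|---|---|---|
| 85% | 84.2% | 83.3% | 80.8% | 76.5% |
| 90% | 89.1% | 88.2% | 85.5% | 81.0% |

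**The 90% threshold.** The early-death share that lifts a true p to a reported 90% is e = 1 - p/0.90.

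- p = 88%: 1 - 0.88/0.90 = 2.2%
- p = 85%: 1 - 0.85/0.90 = 5.6%

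These shares would have to occur among high-risk patients, who are not yet severe. In the first case that means 2.2 of the 12 percentage points of non-recovery. Nothing in the protocol shows that shares of this size occur there.

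**3. Effect on safety.** A dosed patient who dies within 48 h of admission fails criterion 3 and is not in the study. Grade 5 events in that window are therefore zero by construction. Deaths after the window, including those soon after a later first dose, remain and can be graded.

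**The case against.** The strongest reply has five parts.

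- **Safety.** A reader might infer that no fatal event soon after a dose can enter the adverse-event record, and that safety is assessed on survivors only. The protocol does not support that. Criterion 2 admits patients who have died, and the exclusion ends 48 h after admission. The loss is confined to that window.
- **Section 8.2.** A reader might see a direct contradiction between listing death as a failure and excluding early deaths. Failure definitions apply to the patients included, and the failure sentence carries a further clause, so the two can stand together. The direct conflict is between Sections 5.1 and 6.2.
- **Size.** The early-death share is unknown, and some excluded patients may never have been dosed. The only success threshold applies to the class where early death is probably rarest. No reversal of the 90% conclusion can be shown from documented figures. This stands, and it limits the claim to direction and mechanism.
- **Comparison with untreated patients.** Section 11.2.1 names an untreated group. Treated patients must survive to their first dose and untreated patients need not. Deleting the criterion without other provision would add immortal-time bias in favour of Jusvinza. This also stands and restricts the fix. The present rule is only a partial guard, since a patient first dosed on day 5 still counts as treated.
- **Openness.** The restriction is stated, the study is descriptive, and sensitivity tables and safety sets may be left to an analysis plan. Their absence from the protocol is not a fault. The eligibility rule itself is set here, and a plan that starts from the included patients cannot undo it.

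**Conclusion.** The point holds within limits. Criterion 3 removes dosed patients who die within 48 h of admission from the main recovery percentages and from the adverse-event description, contrary to the population in Section 5.1. Among dosed patients the bias has one direction, upward, by the factor 1/(1 - e). At an assumed e of 5% to 10%, a true 60% is overstated by 3.2 to 6.7 percentage points. If no dosed patient died in the window, the bias is zero.

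That the effect is largest in critical patients and smallest in the high-risk group is a clinical expectation, not a documented figure. A reader might conclude that the rule decides whether the 90% target is met; without an early-death rate in the high-risk group, the protocol does not support that. Nor can the rule be defended as a minimum-exposure requirement, because its clock starts at admission.

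**What to change.** 1. For the single-group recovery percentages and the safety description, drop criterion 3. Include every patient with at least one recorded Jusvinza dose and count early deaths as not recovered.
2. Reconcile Sections 5.1, 6.1, 6.2 and 11.2.1 on whether entry depends on prescription or on treatment.
3. Show the result in 48-hour survivors as a labelled sensitivity analysis, with the number of excluded deaths in each severity class.
4. For any comparison with the untreated group, define one common time origin or landmark for both groups, so that removing the criterion does not create immortal-time bias.

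The cost is small: an eligibility line, consistent wording across four sections and one extra table. The records are at the same hospital. The recovery percentages will be somewhat less favourable if any dosed patient died in the window.

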### 8.1.3. Control variables

Because of their possible effect on the therapeutic response, we will consider the following:

- a. Adherence of the patient to the treatment.
- b. Personal pathological history.
- c. Age (years)
- d. Sex (male / female).
- e. Skin color (white, non-white).
- f. Symptomatology (symptomatic, asymptomatic, pre-symptomatic)
- g. Time taken between the positive diagnosis of SARS-CoV-2 and the start of the first symptoms or contact.
- h. Previous treatments and those concomitant with the research product (anti-viral drugs, basic diseases)

---

Approved by:

[name] [name]

Signature:

[figure not shown]

Cargo:

Director of Biomedical Research, CIGB

Date:

13/05/2021

- i. Body mass index.
- j. Toxic habits (smoking, alcohol consumption).

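### Inclusion criterion 4 has no reference date, so in this retrospective study it can exclude patients for joining another trial after Jusvinza was started

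*Protocol*

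**What the plan says.** Section 6.2 of the protocol lists four inclusion criteria. The fourth is "Patients that have not been included in other clinical trials", and that is its full content. The only calendar dates in 6.2 belong to the prescription of Jusvinza: "have been prescribed the treatment with Jusvinza, in the period from March 21 to July 29 of 2021". The third criterion carries its own time limit: "Patients that have not died in the first 48 hours of hospitalization". The fourth has none, and no other section shown supplies one.

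Section 5.1 describes the design: "A retrospective, observational, monocentric study will be carried out with the primary aim of evaluating the effect of Jusvinza in the reduction of inflammation". Section 11.1 makes the analysed number those with information and "complying with the inclusion criteria", so a patient who fails criterion 4 leaves every analysis. Section 8.2 treats progression or death as an individual failure and sets therapeutic success at "90% of the high-risk patients treated with Jusvinza do not reach the severe phases of the disease and then recover". Section 8.1.2 lists the description of adverse events as a secondary variable.

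**The concern.** In a prospective trial, a rule against participation in other trials is judged at enrolment, before any outcome exists. There is no enrolment here. Someone reads a chart and decides whether the patient qualifies, with later events in view. Section 6.2 itself shows this, because criterion 2 admits patients who have already died and criterion 3 looks at survival after admission.

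In that setting an undated criterion 4 covers trial entry at any time, including entry after Jusvinza was given and the patient deteriorated. Exclusion would then depend on something that happened after treatment began and that may be related to treatment failure. The recovery percentages in section 8.1.1, the 90% criterion in 8.2 and the adverse-event description would all lose those patients. Nothing in the protocol asks for the number removed or their outcomes. Two abstractors could also classify the same chart differently. The results are meant for the product's registration dossier (section 14.1.1), so the composition of the denominator matters.

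**Working it through.** **Textual check.** The protocol gives no sample size and no count of patients in other trials, so there is no stated figure to reproduce. The question is whether any text fixes the timing of criterion 4.

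- Section 6.2, criterion 2: dates are given, but for the Jusvinza prescription.
- Section 6.2, criterion 3: a 48-hour limit, counted from hospitalization.
- Section 6.2, criterion 4: no date, window or link to the first dose.
- Sections 5.1 and 11.1: retrospective design, with the analysed set defined by the inclusion criteria.
- Section XIII: data collection runs to September 2021, after the prescription window closes on July 29.

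The timing is therefore open, and the literal reading reaches events after treatment start.

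**Illustration with counts.** Assume 100 high-risk treated patients, of whom 88 recover without progression and 12 fail. Remove k failures and no recoveries. The observed percentage is 88 / (100 − k).

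| k removed | Calculation | Observed | Reaches 90%? |
|---|---|---|---|
| 0 | 88/100 | 88.0% | no |
| 1 | 88/99 | 88.9% | no |
| 2 | 88/98 | 89.8% | no |
| 3 | 88/97 | 90.7% | yes |
| 4 | 88/96 | 91.7% | yes |

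**General form.** Let p be the true recovery rate and f the share of failures removed, with no recoveries removed. Then observed = p / (p + (1 − p)(1 − f)). Setting this to 0.90 gives f = 1 − (p/9)/(1 − p).

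- p = 0.88: f = 1 − 0.0978/0.12 = 18.5%.
- p = 0.85: f = 1 − 0.0944/0.15 = 37.0%.

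The 85% is borrowed from the figure for severe patients in section 3.3 and serves only as an illustrative rate. At p = 0.85, removing 10%, 20%, 30% or 40% of failures gives 86.3%, 87.6%, 89.0% or 90.4%.

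**Direction.** Now let a share g of recoveries be removed as well: observed = p(1 − g) / (p(1 − g) + (1 − p)(1 − f)). With p = 0.85:

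- f = 20%, g = 20%: 0.68 / (0.68 + 0.12) = 85.0%, no bias.
- f = 30%, g = 10%: 0.765 / (0.765 + 0.105) = 87.9%, upward.
- f = 10%, g = 30%: 0.595 / (0.595 + 0.135) = 81.5%, downward.

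The bias is upward only when f exceeds g.

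**The case against.** The strongest reply is that this is a common kind of entry criterion, and that many readers would take it to mean prior or concurrent participation. The protocol does not show that another trial was recruiting these patients, or that anyone treated with Jusvinza moved into one. Both points are fair. They limit what can be said about size but do not supply the missing date. If the benign reading was intended, one sentence secures it.

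Excluding participants in other trials also has a legitimate purpose, since another investigational product would confound the outcome. That stands, and it is why the proposal keeps the criterion up to the first dose and asks for a sensitivity result afterwards. Retaining later entrants has its own risk: a recovery produced by the other product would be counted as recovery after Jusvinza.

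Three stronger readings might be inferred, and the protocol does not support them.

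- A reader might see a contradiction with section 5.1, which includes "All patients with available information that have been treated with Jusvinza, according to the action protocol". That is a general design statement. Eligibility criteria ordinarily narrow such a statement, and section 11.1 says that the criteria apply.
- A reader might argue that the exclusion is unnecessary because section 8.1.3(h) lists "Previous treatments and those concomitant with the research product". Recording a treatment does not remove its effect from simple recovery percentages.
- A reader might conclude that the criterion does favour the product. That requires failures to enter other trials more often than recoveries, which is plausible but documented nowhere.

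**Conclusion.** The point holds in a conditional form. As written, criterion 4 permits exclusion for an event after treatment start, and in a retrospective study that is a weakness in the rule itself. Eligibility is fixed in the protocol, so it should be mended there.

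Whether any bias follows is unknown. The number of patients affected may be zero. Upward bias requires that patients who worsen enter other trials more often than those who recover. Under that condition, and with an assumed 88% true rate in 100 patients, three removed failures carry the result past 90% while one or two do not. At an assumed 85%, about 37% of failures would have to be removed. These figures show that the success criterion can be sensitive to a few exclusions when the true rate lies near the threshold. They do not estimate an actual effect. The change is worth making because it is cheap and closes the ambiguity.

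**What to change.** 1. Reword criterion 4 so that it excludes only patients who participated in another interventional trial on or before the date of the first Jusvinza dose.
2. Keep patients who entered a trial after that date in every denominator and in the safety set. Record the entry date, and count progression that preceded entry as progression.
3. Show a sensitivity result without these later entrants, because recovery after entry may reflect the other product.
4. Report how many patients criterion 4 excluded, and their outcomes.

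The cost is one reworded sentence, one date field on the data recording form, one additional result and one line in the patient accounting. The downside is that later outcomes of retained patients may be influenced by another product. The recorded date and the sensitivity result make that visible but do not remove it. Section 11.2.1 also names a group not treated with Jusvinza. If that group is analysed, it needs an equivalent reference date, since it has no first dose.
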